### Objective and design

2.1

The primary purpose of this study is to verify the effectiveness and safety of CMT in combination with Western medicine therapy for COPD. The patients receiving COPD treatments are randomized into two groups: the experimental group for a combination of CMT and Western medicine therapy and the control group for Western medicine therapy only, while the intervention is performed for 8 weeks, once a week. The study will be conducted as a prospective, single-center, single-blinded, exploratory clinical study, and based on the results, the sample size for future large-scale clinical trials will be determined. The feasibility of the study protocol will also be evaluated. A flow diagram of this study is shown in Figure 1.

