### Randomization, allocation, and blinding

2.2

The patients are randomized into two groups: the experimental group (standard Western medicine therapy + CMT) and the control group (standard Western medicine therapy), in a 1:1 ratio. For randomization, an independent statistician produced a random number table using Microsoft Windows SAS ver. 9.1.3 (SAS Institute Inc, NC, Cary) and allocates random numbers to the patients.

The random number table produced using the SAS and the allocation table for the test or the control group based on the random numbers are stored by the statistician until discontinuation or termination of the study, while the principal investigator does not request for the data.

The subjects in this study are given the screening number as they submit the signed written consent for participation in the clinical study after receiving an explanation regarding the study.

The subjects finally selected through the screening test are given the registration number, and based on the random number table stored by the statistician, each subject is allocated to the group in line with the subject registration number. This study aims to investigate CMT as an add-on to standard drug therapy, and it will be conducted as a single-blinded study with a control group receiving only standard drug therapy. Neither the subjects nor the Korean medicine doctor practitioners is blinded. The principal investigator and assessor who collecting the data are blinded to each group allocation.

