#### Primary outcome

2.5.1

Primary outcome is the 6-minute walk test (6-MWT). The 6-MWT is a relatively simple and economic test that measures the distance the patient can walk on a flat, hard surface for 6 minutes. The test is commonly used to assess motor function in COPD patients,^[19]^ and it has been regarded as a crucial indicator of exercise tolerance in COPD patients across numerous studies.^[20–23]^

The clinical trial process in presented in Table 1.

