### Sample size

2.7

This study is a small-scale, prospective, preliminary clinical study to verify the feasibility and treatment effects of a large-scale clinical trial. Therefore, an accurate sample size must not be determined. Based on a previous study suggesting a minimum of 12 subjects per group for a pilot study in biomedical science,^[28]^ the number of subjects to be recruited and the minimum range for efficacy evaluation is set as 16, considering a 20% dropout rate, a total of 40 subjects will be recruited.

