### Statistical methods

2.11

Statistical significance is based on the significance level 0.05 with a power of 0.8.

Intended to treat, ITT: The subjects who underwent CMT at least once and performed the 6-MWT as the primary outcome.Per protocol, PP: The subjects who received the CMT intervention up to 80% or higher and performed the relevant tests.For all analyses, the ITT is the main analysis, while the PP is carried out simultaneously, and their results are presented together.

For continuous variables, the results are presented as mean and standard deviation, for which an independent *t* test or Mann–Whitney *U* test will be carried out. If the normality assumption is satisfied, an independent *t* test will be carried out; otherwise, the Mann–Whitney *U* test will be carried out. To adjust for the influence of age, ANCOVA with age as a covariate will be carried out. If a significant intergroup difference is found related to the baseline values, ANCOVA with age and baseline as covariates will be carried out. For missing values, the last measured value will be used for each subject based on the last observation carried forward (LOCF).

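### The planned ANCOVA adjusts for baseline 6-MWT only after a significant baseline test, so chance picks the covariates and precision is usually lost

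*Protocol article*

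**What the plan says.** All of the following is in the protocol article. The section Statistical methods gives a two-group test for continuous outcomes, a t test if normality holds and "otherwise, the Mann–Whitney" test. It then plans a model with a single covariate: "To adjust for the influence of age, ANCOVA with age as a covariate will be carried out". The outcome's baseline is added only on a condition: "If a significant intergroup difference is found related to the baseline values, ANCOVA with age and baseline as covariates will be carried out". The only significance level given is in the same section: "Statistical significance is based on the significance level 0.05 with a power of 0.8".

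Under Primary outcome: "Primary outcome is the 6-minute walk test (6-MWT"). Neither section says whether the final distance or the change from baseline is compared. Nothing elsewhere provides for unconditional baseline adjustment. The section attaches the label of main analysis to the ITT set and calls none of the listed tests or models primary.

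Objective and design says that "based on the results, the sample size for future large-scale clinical trials will be determined".

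**The concern.** Groups formed by randomisation differ at baseline only by chance, so a significance test of the baseline difference says nothing about whether the covariate is needed. What makes a covariate useful is how well it predicts the outcome, and that does not depend on the baseline p-value. Here age, whose relation to the outcome is not quantified, is always in the model. Baseline walking distance, which one would expect to predict later walking distance well, is usually out.

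Three things are at stake in a trial of 40 patients:

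- precision that would cost no extra patients;
- protection against baseline imbalances that are sizeable but not significant;
- a stable residual variance to carry into the sample size of the larger trial.

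**Working it through.** **Inputs from the document.** Level 0.05 (two-sided assumed, since sidedness is not stated). Allocation: "the control group (standard Western medicine therapy), in a 1:1 ratio". Numbers: "is set as 16, considering a 20% dropout rate, a total of 40 subjects will be recruited", with 16 read as evaluable per group.

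**The plan's own figure.** 16 / (1 − 0.20) = 20 per group, 40 in total. This reproduces. The stated power of 0.8 cannot be reproduced, because no effect size or SD is given.

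**Assumptions not in the document.** Normal data; correlation r between baseline and final value of 0.5 to 0.9; age correlated −0.3 with baseline; true effect 0.5 SD.

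**Step 1: how often baseline enters.** For one test, P(not significant) = 1 − 0.05 = 95%. The simulated trigger rate was 4.8% to 5.1%. If any of k independent baseline values could trigger the rule, the rate is 1 − 0.95^k, for example 1 − 0.95^5 = 23%.

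**Step 2: what leaving it out costs.** Adjusting a final value for baseline multiplies its residual variance by 1 − r². For change analysed without baseline, the variance relative to ANCOVA is 2(1 − r)/(1 − r²).

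| r | 1 − r² | change variance / ANCOVA variance |
|---|---|---|
| 0.5 | 0.75 | 1.33 |
| 0.7 | 0.51 | 1.18 |
| 0.8 | 0.36 | 1.11 |
| 0.9 | 0.19 | 1.05 |

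**Step 3: power, 20 per arm.** The rule fits age plus baseline if the baseline p-value is below 0.05 and age alone otherwise. The comparator always fits both.

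| r | Final value, rule | Change, rule | Baseline always in |
|---|---|---|---|
| 0.5 | 36% | 33% | 42% |
| 0.7 | 36% | 50% | 56% |
| 0.8 | 36% | 68% | 71% |
| 0.9 | 38% | 93% | 93% |

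A run of 40,000 trials per setting agrees to within about 2 points. With 16 per arm that run gives, for final values, 28/28/29/30% under the rule against 34/45/59/86% with fixed adjustment. For change it gives 28/42/57/85% against 34/46/59/86%.

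**Step 4: type I error over all trials, 20 per arm.** For final values the rule gives 0.044, 0.039, 0.035 and 0.026 at r = 0.5, 0.7, 0.8 and 0.9. For change it gives 0.045, 0.047, 0.048 and 0.050. Fixed adjustment gives about 0.05 throughout.

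**Step 5: trials with a moderate, non-significant imbalance.** With 20 per arm the baseline test is significant only beyond t(38 df) × √(2/20) = 2.024 × 0.316 = 0.64 SD. An imbalance just short of that stays in the model unadjusted. Ignoring age, it shifts a final-value estimate by about r × 0.64, which is 0.45 SD at r = 0.7 and close to the assumed effect. It shifts a change estimate by about (1 − r) × 0.64 = 0.19 SD in the opposite direction. In null trials with baseline p between 0.05 and 0.20 (0.20 − 0.05 = 15% of trials), final-value false positives are about 8% at r = 0.5, rising to about 12%, against about 5% with fixed adjustment. For change at r = 0.7 the rate is about 7%.

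**Step 6: sizing the next trial.** Sample size is proportional to variance. On final values at r = 0.7, a trial sized from the age-only residual variance would be 1/0.51 = 1.96 times as large as one sized from the baseline-adjusted variance. Under the rule, a chance test decides which of the two variances the pilot's ANCOVA reports.

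**The case against.** The strongest counter-argument is that the large losses hold only for final values. If change is analysed, most of the precision is already captured at r of 0.7 or more. The gain from fixed adjustment is then 6 points at 0.7, 3 at 0.8 and nil at 0.9. The document does not settle which form is used, so the size of the loss is open. It also gives no correlation or effect size, so every power figure is conditional on assumptions. This all stands, which is why both forms and r = 0.5 are shown.

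A reader might infer from Step 5 that the rule produces too many false positives. It does not: averaged over all trials its type I error is at or below nominal. The excess belongs to the 15% of null trials with a moderate imbalance, and it shrinks on change scores as r rises.

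A reader might also infer that the trial's main analysis discards baseline. The document does not support that, because the label applies to the ITT set and no model is named primary. What can be said concerns the planned ANCOVA.

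The 95% assumes one test on baseline 6-MWT. The text speaks of baseline values in the plural, and a wider trigger would fire more often. The ITT set is also restricted after randomisation, so 5% is exact only for the groups as randomised. Neither point stops the data from choosing the model.

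Finally, this is a 40-patient exploratory pilot without a formal power calculation. That lowers the severity but does not remove the point: Objective and design also sets out to verify effectiveness and to size a larger trial from the results.

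**Conclusion.** The concern holds as a weakness in how the covariates are chosen. The rule as written leaves baseline 6-MWT out of the ANCOVA in about 95% of properly randomised trials, assuming a single two-sided test at 0.05. It does not bias the estimate on average and is not anti-conservative overall.

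The cost is efficiency and stability. With 20 per arm and a 0.5 SD effect, the power loss runs from 6 points (r = 0.5) to 55 points (r = 0.9) on final values, and from 9 points (r = 0.5) to none (r = 0.9) on change. In addition, the residual variance available for planning depends on a chance result. These sizes rest on assumed correlations, an assumed effect and normal data. That the data choose the covariates rests on the protocol's own wording. Severity: should be fixed, not disqualifying for an exploratory pilot.

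**What to change.** Name as the primary analysis one ANCOVA of end-of-treatment 6-MWT distance on arm, baseline 6-MWT distance and age, fitted whatever the baseline comparison shows. Do the same for each continuous secondary outcome with its own baseline. Delete the significance test of baseline differences as a decision step; baseline values can still be described.

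This also removes the ambiguity over final value or change: with baseline in the model, the two give the same arm effect and standard error.

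The cost is one sentence and one degree of freedom (with 40 patients, residual degrees of freedom go from 40 − 3 = 37 to 40 − 4 = 36). No new measurement is needed, since the conditional ANCOVA already uses baseline. The section Trial status reports recruitment as ongoing, so the change could be made before any analysis.

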**Methods:**

This is a randomized, single-blind, single-center clinical pilot trial. Patients with COPD receiving standard drug therapy are randomly divided into an experimental group (n = 20) and a control group (n = 20) at a 1:1 ratio. The experimental group receives CMT adding to the standard medical therapy once a week for 8 weeks. The control group receives only the standard drug treatment. The trial is conducted with an outcome assessor and statistician blinding. The primary outcome is the 6-minute walk test. The secondary outcomes include the pulmonary function test, the Modified Medical Research Council, visual analog scale for dyspnea, COPD assessment test, quality of life using the St. George's respiratory questionnaire, EuroQOL five dimensions questionnaire, and Korean pattern identification questionnaire. Adverse events are also be evaluated.

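### LOCF is the only stated method for missing values: it can bias the 6-MWT contrast either way and gives unreliable effect and SD inputs for the next trial

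*Protocol article*

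**What the plan says.** The protocol article, section 2.11 (Statistical methods), states one rule for missing data: "For missing values, the last measured value will be used for each subject based on the last observation carried forward (LOCF". It names no other method and no sensitivity analysis aimed at missing values. The same section says "For continuous variables, the results are presented as mean and standard deviation". It plans a t test or Mann–Whitney U test, and an ANCOVA on age to which baseline is added only if the arms differ significantly at baseline.

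The main analysis set (ITT) requires at least one CMT session and a performed 6-MWT. A per-protocol analysis, limited to patients with at least 80% of the CMT and the tests done, is reported beside it.

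Section 2.7 (Sample size) allows for losses: "the minimum range for efficacy evaluation is set as 16", and "considering a 20% dropout rate, a total of 40 subjects will be recruited". Section 2.1 (Objective and design) gives the pilot's purpose: "based on the results, the sample size for future large-scale clinical trials will be determined".

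The article does not say whether the 6-MWT is analysed as the final value or as change from baseline. Table 1 (the visit schedule) is not reproduced in the text at hand, so the number of post-baseline walk tests is unknown.

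**The concern.** LOCF assumes that a patient's walking distance stays where it was at the last test, and the analysis then handles that value as if it had been measured. In COPD this is not a safe assumption, least of all for patients who leave because they are getting worse: they keep credit for an earlier, better distance. Section 2.2 leaves patients and practitioners unblinded, and only one arm has the added weekly treatment sessions. Dropout that differs between arms in amount or cause is therefore plausible, and in that situation the direction of LOCF bias cannot be predicted.

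Two things are at stake: the 6-MWT contrast itself, and the effect and SD that the pilot passes on to the full-scale trial.

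**Working it through.** **Inputs from the article.** 16 evaluable per arm and 20% dropout (section 2.7); 20 per arm randomised (abstract); significance level 0.05 and power 0.8 (section 2.11).

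**Inputs assumed.** The article gives no 6-MWT effect, SD or correlation. All distances, SDs and correlations below are illustrations. The significance level is taken as two-sided.

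**1. The plan's own figure.** 16 / (1 − 0.20) = 20 per arm, 40 in total. This reproduces exactly. At that dropout, 0.20 × 20 = 4 patients per arm could need a carried value.

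**2. Bias in the contrast.** Suppose a fraction d has baseline carried forward and dropout is unrelated to outcome. An arm's mean change then becomes (1 − d)μ.

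| True change, CMT / control (m) | Dropout, CMT / control | True contrast (m) | LOCF contrast (m) |
|---|---|---|---|
| 30 / 0 | 20% / 20% | 30 | 0.8×30 − 0.8×0 = 24 |
| −20 / −20 | 10% / 30% | 0 | 0.9×(−20) − 0.7×(−20) = −4 |
| −20 / −20 | 30% / 10% | 0 | 0.7×(−20) − 0.9×(−20) = +4 |
| 0 / 0 | 10% / 30% | 0 | 0 |

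Equal dropout shrinks the contrast by 20%. Unequal dropout can create a contrast of either sign. In this model the bias vanishes only in special cases, such as no mean change in either arm. Dropout caused by worsening lies outside this formula and adds bias of its own.

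**3. SD of change.** Under the same model the variance of change is (1 − d)σ² + d(1 − d)μ². With d = 0.20:

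- μ = 0: 0.80σ², SD ratio 0.894 (about 11% low)
- μ = 0.5σ: 0.80 + 0.16×0.25 = 0.84σ², SD ratio 0.917 (about 8% low)
- μ = 1σ: 0.96σ², SD ratio 0.980
- μ = 1.118σ: 1.00σ², no understatement
- μ = 1.25σ: 1.05σ², SD ratio 1.025 (overstated)

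**4. Other SDs.** These come from a simulation with 1,000,000 draws per setting, baseline SD 100 m, mean rise 15 m, correlation 0.7 to 0.9 and 20% carried from baseline. The baseline-adjusted residual SD falls to about 0.90 to 0.91 of its true value (for example 60.1 to 54.7 m at correlation 0.8). The SD of the endpoint value hardly moves: 100 against 100 m with equal visit SDs, and about 108 against 110 m if the final SD is 10% larger. The ratio is 0.98 to 1.00.

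**5. Effect on the next trial.** Assume a true effect of 30 m and a change SD of 60 m, with n per arm = 2(1.960 + 0.842)²σ²/δ² = 15.70σ²/δ².

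- Correct inputs: 15.70 × 3,600 / 900 = 62.8, so 63 per arm.
- LOCF SD, taking a mean change of 15 m (0.25 SD, midway between the arms): variance 3,600 × (0.80 + 0.16×0.0625) = 2,916, SD 54.0 m.
- LOCF SD with the effect kept at 30 m: 15.70 × 2,916 / 900 = 50.9, so 51 per arm. True power is about 71%.
- LOCF SD and the attenuated 24 m together: 15.70 × 2,916 / 576 = 79.5, so 80 per arm.

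For change SDs of 50 and 80 m, the correct figures are 44 and 112 per arm. Using the understated SD alone gives 36 and 90 (power 72% and 71%). Using both LOCF inputs gives 56 and 141.

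**The case against.** A reader might infer that LOCF understates the SD in general and so leads straight to an undersized full trial. The documents do not support that. The understatement applies to change or to a baseline-adjusted residual, and only while mean change is modest. The article does not say that change is analysed, and the planned t test may well use the final value, whose SD is almost unaffected. Nor does undersizing follow: the scenario that lowers the SD also shrinks the effect, and a trial sized on both would be larger than needed (80 against 63 per arm). Section 2.1 says only that the results will determine the sample size, not which results. These objections stand and limit the point.

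It can also be said that 20% carried from baseline is an upper scenario. The 20% is a recruitment allowance. The carried value may be a mid-trial one, and the ITT definition may exclude patients without a post-baseline test instead of giving them zero change. This stands too, although such an exclusion replaces imputation with selection.

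The parallel per-protocol analysis appears to use no imputation. It is a weak check, because it is selected by adherence and does not address why data are missing.

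Finally, further sensitivity analyses are commonly left to an analysis plan that is not shown, so their absence is not held against the article. The choice of LOCF as the only stated rule is different: the article fixes it.

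**Conclusion.** The point holds in limited form. LOCF is the sole stated method for missing values, in a trial that allows for 20% dropout, and it can bias the 6-MWT contrast. At the upper scenario of 20% per arm carried from baseline, an effect is reduced to 0.80 of its size (an assumed 30 m to 24 m). With unequal dropout a false contrast of either sign can appear (±4 m in the illustration).

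The SD of change or the baseline-adjusted residual SD may be about 8 to 11% too low when mean change is at most 0.5 SD. No such claim holds for the endpoint value.

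Effect and SD taken from an LOCF analysis are therefore unreliable inputs for the next trial, but the direction of the net error in its sample size is not determined. In the illustration it runs from 51 to 80 per arm against 63 needed. All distances and SDs are assumptions, and the closed forms take dropout as unrelated to outcome.

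**What to change.** Replace LOCF as the main method in section 2.11.

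- **Several post-baseline 6-MWTs:** use a likelihood-based repeated-measures model with arm, visit, arm-by-visit, baseline and age.
- **Only one post-baseline 6-MWT:** use an ANCOVA on observed data with baseline and age as covariates. Add multiple imputation only if useful auxiliary data exist; imputing from arm, baseline and age alone adds essentially nothing to that ANCOVA.
- **Sensitivity:** neither approach removes bias from worsening that was never observed. Add one analysis that lets dropouts do worse than comparable completers. Keep LOCF at most as a labelled sensitivity analysis.
- **Next trial:** take the planning SD from observed or model-based values, and state whether it is the SD of the endpoint value, of change, or of the baseline-adjusted residual.

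The cost is a little more analysis work and a slightly wider interval. No new data are needed, and section 3.1 reports recruitment as ongoing, so the change can be made before analysis.

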## Discussion

3

The present protocol is the first attempt in South Korea to verify the effectiveness and safety of CMT for COPD. The effects of respiration rehabilitation are widely known, and exercise therapy is actively applied in clinical practice for the management of functional abilities in COPD patients.^[1]^ Exercise therapy is the optimal management therapy among non-pharmacological therapies, and it plays a role in improving the quality of life of COPD patients by improving symptoms such as dyspnea.^[29]^ However, voluntary participation in exercise therapy is not easy for patients with severe breathing difficulties. Therefore, the interest in MT performed by experts is increasing, and studies on COPD with MT have been conducted.^[14–18]^ MT plays a role in expanding the rib cage and reducing respiratory muscle shortening.^[30]^ Studies have shown a major effect on the improvement of motor performance in patients with COPD.^[16]^ The CMT used in this study is a technique involving 10 to 15 minutes of exercise conducted by a trained professional Korean medicine doctor, and as the patient can receive the therapy while lying on the bed, the technique is advantageous in that it can be performed regardless of the severity of the patient.

The results of randomized controlled trial (RCT) based on this protocol are anticipated to contribute to promoting the research on CMT in COPD treatment as well as being the starting point in establishing the clinical basis. Furthermore, the addition of an effective treatment for COPD, a chronic, intractable disease, will prove useful for clinicians and in the management of COPD patients.

